## Abstract

**Aim::**

To describe the protocol for a multi-centre randomised controlled trial to determine whether treatment protocols monitoring daily CRP (C-reactive protein) or PCT (procalcitonin) safely allow a reduction in duration of antibiotic therapy in hospitalised adult patients with sepsis.

**Design::**

Multicentre three-arm randomised controlled trial.

**Setting::**

UK NHS hospitals.

**Target population::**

Hospitalised critically ill adults who have been commenced on intravenous antibiotics for sepsis.

**Health technology::**

Three protocols for guiding antibiotic discontinuation will be compared: (a) standard care; (b) standard care + daily CRP monitoring; (c) standard care + daily PCT monitoring. Standard care will be based on routine sepsis management and antibiotic stewardship. Measurement of outcomes and costs. Outcomes will be assessed to 28 days. The primary outcomes are total duration of antibiotics and safety outcome of all-cause mortality. Secondary outcomes include: escalation of care/re-admission; infection re-lapse/recurrence; antibiotic dose; length and level of critical care stay and length of hospital stay. Ninety-day all-cause mortality rates will also be collected. An assessment of cost effectiveness will be performed.

**Conclusion::**

In the setting of routine NHS care, if this trial finds that a treatment protocol based on monitoring CRP or PCT safely allows a reduction in duration of antibiotic therapy, and is cost effective, then this has the potential to change clinical practice for critically ill patients with sepsis. Moreover, if a biomarker-guided protocol is not found to be effective, then it will be important to avoid its use in sepsis and prevent ineffective technology becoming widely adopted in clinical practice.

## Background and rationale

Early, appropriate antimicrobial treatment for infection is a crucial part of emergency interventions aimed at improving sepsis survivorship.^
1
^ Choosing the right antimicrobial drugs and doses is crucial because inappropriate antibiotic therapy is associated with two-to-fourfold increase in risk of death under these circumstances.^
2
^

Once commenced, the optimum duration of antibiotic treatment is less certain.^
3
^ Fixed duration antibiotic courses (up to 14 days in some circumstances) have been widely used in the NHS because clinical signs and microbiology culture tests are not sufficiently useful for monitoring treatment efficacy in order to guide the decision to stop the administration of antibiotics.^
4
^ Daily clinical review of treatment and patient progress, performed alongside microbiology results and advice, do provide opportunities to limit patient exposure to broad-spectrum antibiotics while tailoring effective therapy for a proven infection – the so-called ‘Start smart - then focus’ approach.^4,5^

Readily available circulating serum proteins such as C-reactive protein (CRP) and procalcitonin (PCT) – the most intensively researched biomarkers – are often raised in sepsis and usually fall in response to effective treatments.^
6
^ This provides a potential opportunity to personalise the duration of antibiotic therapy which could lead to reductions in population antibiotic usage, adverse effects for patients, improved healthcare resource utilisation and downstream benefits relating to antimicrobial resistance – an urgent priority. These biomarkers, however, are part of a complex inflammatory response triggered not only by infection but by other stimuli such as trauma and surgery. Thus, unnecessarily prolonged antibiotic treatment may be commenced if guided solely by raised levels of these biomarkers as part of antibiotic initiation/escalation protocols.^
7
^ Alternatively, biomarker-guided antibiotic discontinuation protocols for critically ill patients have been associated with shorter treatment durations in some healthcare systems internationally^1,8^ and reduced mortality,^
9
^ but studies are at high risk of bias^1,8,9^ and with uncertain relevance to NHS practice.^
10
^ There is thus a need for a multicentre randomised controlled UK trial to determine whether an antibiotic treatment protocol based on monitoring CRP or PCT might safely allow a reduction in the duration of antibiotic therapy in patients with sepsis.

## Objectives

### Primary objective

To determine whether treatment discontinuation protocols based on monitoring CRP or PCT in hospitalised adult patients with suspected sepsis reduces the duration of antibiotic therapy compared with standard care while maintaining treatment safety as measured by mortality 28 days after randomisation.

### Secondary objectives

To determine adherence to biomarker treatment protocols and their effects on antibiotic consumption, infection and antibiotic adverse events, critical care and hospital length of stay, acquisition cost of antibiotics, longer-term mortality and cost-effectiveness in the NHS setting.

## Methods

### Trial design

This is a multicentre prospective, individual patient randomised, 3-arm, controlled, intervention-concealed clinical and cost effectiveness trial. The trial is managed by the Warwick Clinical Trials Unit and sponsored by the University of Manchester. The funding is provided by the National Institute for Health Research (NIHR) following a commissioned call from the Health Technology Assessment programme (15/99/02). The NHS main contractor is the Northern Care Alliance NHS Foundation Trust. The trial is coordinated by a Trial Management Group (TMG) and independent oversight is provided by a Trial Steering Committee (TSC) and a Data Monitoring Committee (DMC). The trial has been designed and will be reported in line with the CONSORT (Consolidated *S*tandards *o*f *R*eporting *T*rials) statement.^
11
^ Trial conduct has been planned in full conformance with the principles of the Declaration of Helsinki and Good Clinical Practice.

### Study setting

The trial was planned to take place in at least 32 acute care NHS hospitals with adult critical care units. Hospitals must provide evidence that they are able to participate in critical care research, have access to the relevant patient population, have routine clinical biochemistry services able to provide, or establish, daily CE-marked PCT and CRP quality-assured laboratory assays.

### Participant inclusion criteria

Hospitalised adult patients at least 18 years of ageUp to 24 h of initiation of empiric intravenous antibiotic treatments for a suspicion of sepsis^
12
^Likely to remain hospitalised and receiving intravenous antibiotic treatment for at least the next 72 h; andRequirement for critical care.

A 24-h recruitment window from initiation of antibiotics for sepsis is required to determine baseline biomarker values to guide subsequent protocolised treatment duration advice.^6,10^

### Participant exclusion criteria

Prolonged (greater than 21 days) antimicrobial therapy (e.g. for endocarditis, cerebral/hepatic abscess, tuberculosis, osteomyelitis);Severely immunocompromised not caused by sepsis (e.g. neutropenia less than 500 neutrophils/µl);Any patient given, or anticipated to receive an IL-6 receptor inhibitor drug (e.g. tocilizumab or sarilumab) during their acute hospital admission;All treatments for suspected sepsis likely to be stopped within 24 h of its initiation because of futility;Consent declined; orPreviously enrolled into this trial.

Co-enrolment of study participants into other trials will be considered by the TMG using national guidance.^
13
^

### Trial protocol

Blood will be drawn daily in every trial patient participant from randomisation until discontinuation of antibiotics for the sepsis episode or discharge from hospital. The clinicians responsible for managing patients will receive daily standardised advice from the local research team on either standard care or on biomarker-guided antibiotic discontinuation. Advice will be based on daily serum testing of either (a) PCT or (b) CRP or (c) ‘no test’ (control group). The antibiotic discontinuation protocols are described alongside the standardised written advice for each group in Figure 1.

**Figure 1. fig1-17511437231169193:**
[figure not shown]
Trial biomarker-guided antibiotic discontinuation protocol.

### Trial interventions

Procalcitonin arm. Standard care with daily serum PCT measurement until antibiotic discontinuation or hospital discharge. Daily feedback to clinical team based on PCT discontinuation protocol (Figure 1).CRP arm. Standard care with daily serum CRP measurement until antibiotic discontinuation or hospital discharge. Daily feedback to clinical team based on CRP discontinuation protocol (Figure 1).

For the randomly allocated intervention arms, patient research blood collection (minimum of 2 ml research sample per day) and serum biomarker laboratory testing (PCT or CRP) will commence within the first 24 h following the initiation of intravenous antibiotics for sepsis. Daily research blood sampling, laboratory testing and subsequent advice in every patient will continue until antibiotics for the sepsis episode have been discontinued. Research blood sampling will not recommence if antibiotics are subsequently re-introduced within the 28-day study period following patient randomisation. If a participant is discharged from hospital on a course of antibiotics for the initial sepsis episode, the trial intervention will cease at the time of discharge. Phlebotomy and samples will be handled in line with agreed local standard care practice.

### Standard care

Daily blood sampling and delivery of sample to the laboratory. No biomarker testing of sample and feedback to clinical team will be based on usual care protocol (Figure 1).

Patients recruited to both control and intervention arms will receive standard NHS care for sepsis and antibiotic stewardship will follow Public Health England (PHE) guidance.^
5
^ Patients will be reviewed daily by their medical team with documented decisions on antibiotic treatment guided by standard clinical assessment and review of microbiological culture results. Routinely available laboratory data, such as white blood cell counts, will remain part of standard care for all patients recruited to our proposed trial because these are part of the current standard of NHS care for patients with sepsis.^
5
^ Daily clinical review of all patients with sepsis, as a standard-of-care, will allow incorporation of the intervention protocols for daily assessment of antibiotic discontinuation described in Figure 1.

### Outcome measures

#### Primary outcome measures

Clinical effectiveness: Total duration (measured in days) of antibiotic treatment to 28 days following randomisationSafety: 28-day all-cause mortality following randomisation

#### Secondary outcome measures

Effectiveness and safety outcome measures to 28 days following randomisation:

Antibiotic duration (measured in days) and dose (measured as Defined Daily Dose) for the sepsis episodeTotal antibiotic dose (measured as Defined Dailey Dose)Unscheduled care escalation/re-admissionInfection relapse/recurrence requiring further antibiotic treatmentSuper-infection defined as new infection at a different anatomical siteSuspected clinically relevant antibiotic adverse reactionsTime to ‘fit’ for hospital discharge

All-cause mortality will be determined at 90 days

Health care system benefit outcomes

Assessment of in-trial cost effectiveness (see below)Critical care unit length and level of stay^
14
^Hospital length of stay (days)

Safety reporting

Adverse event data (see Supplemental Material)

#### Sample size estimate

A total sample size of 2760 will be required to detect both a mean of 1-day (0.93 days to be precise) reduction in antibiotic duration (using a mean antibiotic duration of 7 days, a pooled standard deviation of 6 days, 90% power, a significance level of 5%, with a 5% withdrawals rate) and a non-inferiority safety margin of 5.4% (using a 1-sided significance level of 2.5%, 90% power and 5% withdrawal rate) assuming 28-day mortality is 15% in both arms (see Supplemental Material).

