### Randomisation, stratification and allocation concealment

Patient participants will be allocated at random to PCT, CRP and usual care groups in a 1:1:1 ratio using a computer-generated randomisation sequence produced by the minimisation method. Stratification factors will be (i) sepsis severity (sepsis or septic shock^
12
^), (ii) recruitment centre and (iii) surgery within the last 72 h or not. Allocation concealment will be provided by a centralised 24-h web-based randomisation system located at Warwick Clinical Trials Unit.

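### The 90% power is stated for each primary outcome separately; at 2760 patients the power to show both for one biomarker is about 80%, and mortality alone has 88.5%

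*Protocol article*

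**What the plan says.** The Primary objective section asks whether a protocol guided by CRP or PCT "reduces the duration of antibiotic therapy compared with standard care while maintaining treatment safety as measured by mortality 28 days after randomisation". The Conclusion of the abstract ties a change in practice to a protocol that "safely allows a reduction in duration of antibiotic therapy" and is also cost effective. The Primary outcome measures section names two outcomes: antibiotic duration to 28 days (clinical effectiveness) and 28-day all-cause mortality (safety).

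The Sample size estimate section covers both in one sentence: "A total sample size of 2760 will be required to detect both a mean of 1-day" reduction and the mortality margin. The duration part is "0.93 days to be precise) reduction in antibiotic duration", with "a pooled standard deviation of 6 days, 90% power, a significance level of 5%, with a 5% withdrawals rate". The mortality part is "a non-inferiority safety margin of 5.4% (using a 1-sided significance level of 2.5%, 90% power and 5% withdrawal rate"; the true death rate by day 28 is taken to be 15% in each group. Patients are "allocated at random to PCT, CRP and usual care groups in a 1:1:1 ratio". The article gives no power for the two outcomes together.

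**The concern.** The objective is a conjunction: shorter treatment and maintained safety, for the same biomarker. A total said to be enough to detect both effects, with 90% beside each, is easily read as 90% power for the objective. Two separate 90% calculations do not give that. The chance of missing a protocol that is truly effective and safe would be about 20%, against the 10% that such a reader would infer.

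The mortality bracket also claims 90% power after 5% withdrawal, and that can be checked directly.

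**Working it through.** **Inputs** (Sample size estimate and Randomisation sections): total 2760; allocation 1:1:1; withdrawal 5%; duration difference 0.93 days, SD 6 days, significance level 5% (taken as two-sided, which reproduces the total); mortality 15% in both arms, margin 5.4 points, one-sided 2.5%. The correlation between the two test statistics is not given and is an assumption here.

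**Patients per arm.** 2760 / 3 = 920 randomised; 920 × 0.95 = 874 evaluable.

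**Reproducing the stated total.** The multiplier is (1.960 + 1.282)² ≈ 10.51.
- Duration: n = 2 × 6² × 10.51 / 0.93² ≈ 875 per arm. Dividing by 0.95 gives 922 per arm, 2766 in total; multiplying by 1.05 instead gives 919 per arm, 2757 in total. Both agree with 2760.
- Mortality: n = 2 × 0.15 × 0.85 × 10.51 / 0.054² ≈ 919 per arm, 2757 in total, before any withdrawal. Allowing for 5% withdrawal gives 968 per arm, 2904 in total. So 2760 matches the mortality calculation only with no withdrawals.

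**Marginal power at 874 per arm.**
- Duration: SE = 6 × √(2/874) = 0.287; 0.93/0.287 − 1.960 = 1.280; power Φ(1.280) = 90.0%.
- Mortality: SE = √(2 × 0.15 × 0.85/874) = 0.01708; 0.054/0.01708 − 1.960 = 1.201; power Φ(1.201) = 88.5% (88.2% by the Farrington-Manning method).
- Margin giving 90% mortality power: 3.24 × 0.01708 = 5.5 points at 874 per arm, and 5.4 points at 920 per arm.

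**Joint power for one biomarker against standard care.** Independence gives p₁ × p₂. For other correlations the figure is the bivariate normal probability that both tests succeed.

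| Correlation (assumed) | Joint power at 874 per arm |
|---|---|
| −0.8 | 78.5% |
| −0.3 | 78.9% |
| 0 | 0.8998 × 0.8852 = 79.6% |
| +0.3 | 80.9% |
| +0.8 | 84.6% |

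**Bounds under any dependence.** The lower bound is p₁ + p₂ − 1 = 0.8998 + 0.8852 − 1 = 78.5%. The upper bound is the smaller marginal power, 88.5%.

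**On the stated 90% and 90%.** Independence gives 0.90 × 0.90 = 81%, and the floor is 0.90 + 0.90 − 1 = 80%.

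**Sensitivity.** If the true reduction were the rounded 1.0 day, duration power would be 93.6% and joint power 82.9% under independence.

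**The case against.** The strongest reply is that the article does not misstate joint power. Each 90% stands in its own bracket, attached to its own outcome, and a careful reader can see that it is marginal. Powering each primary outcome separately is common practice. The article sets out no formal decision rule; the rule is read from the objective and from the word both. The section refers to supplemental material, not shown here, which may give a rule or a joint power. All of this stands, and it limits the point to how the power is described.

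It can also be said that the abstract's conclusion adds cost effectiveness, so two outcomes are not the whole claim. That sentence is wider, but the primary objective and the sample size sentence concern exactly these two outcomes.

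A further reply is that the mortality shortfall is a separate matter from joint power. It is, which is why the joint figure is also given on the stated 90% and 90%; it falls from 81% to 79.6% when the shortfall is included.

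The reply does not remove two facts. The sentence offers 2760 as enough for both effects without saying how likely it is to show both. And the 90% for mortality does not follow from the stated margin and withdrawal rate.

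A reader might go further in two ways that the documents do not support:
- That both biomarkers must succeed. The objective says CRP or PCT, so the relevant power is the one for each biomarker.
- That a negative conclusion is weakened. The article's negative conclusion concerns a protocol not found to be effective. Duration is the outcome labelled clinical effectiveness, and its marginal power is 90.0%.

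**Conclusion.** The point holds as a matter of stated power; it does not make 2760 an invalid sample size. For one biomarker, the power to show both a shorter duration and non-inferior mortality is about 80%. The central value of 79.6% assumes independent test statistics, a true reduction of 0.93 days and equal true mortality of 15%. With these marginal powers no correlation brings it to 90%, since it cannot exceed 88.5% or fall below 78.5%. The mortality power after the stated 5% withdrawal is 88.5%, a shortfall of 1.5 points. That both results are required is inferred from the primary objective and the sample size sentence, since the article sets no formal rule.

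**What to change.** In the Sample size estimate section:
- Label the power for each outcome as marginal.
- Correct the mortality power to about 88.5% after 5% withdrawal.
- Add that 2760 patients give about 80% power per biomarker to show both outcomes, under independence, with bounds of 78.5% to 88.5%.

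If the supplemental material already contains a joint figure, carry it into this paragraph. Because both tests must succeed, each can keep its full significance level, with no alpha split between the two outcomes within a biomarker.

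The cost is a few restated figures and a less favourable stated power. No patients are added and the analysis does not change.

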**Figure 2. fig2-17511437231169193:**
[figure not shown]
Trial flow diagram.

**Table 1. table1-17511437231169193:** Schedule of delivery of trial interventions and data collection.

Visit day	1				2				3	4	5	6	7	8–28
Screening	✓													
Informed Consent (Patient consent/ Consultee /Guardian/Welfare Attorney/ Retrospective Patient Information & consent)	Patient / Consultee (Guardian/Welfare Attorney) Opinion/consent will be obtained initially. Retrospective patient consent will be obtained when/if the patient has recovered mental capacity during acute hospital care.													
Medical history and baseline characteristics	✓													
Inclusion/exclusion criteria	✓													
Randomisation	✓													
Baseline research blood sample	✓													
Intervention								Biomarker-guided antibiotic discontinuation						
SOFA score	✓								✓				✓	
Adverse events					✓				✓	✓	✓	✓	✓	✓
Follow-up														
Daily collection of clinical information, infection status, antibiotic use and care environment	✓				✓				✓	✓	✓	✓	✓	✓
Final visit	*If the patient is discharged to another hospital or to the community within 28 days following randomisation, the local research team will contact the patient and their treating health care professional (hospital physician or General Practitioner) to collect outstanding information about the stated primary and secondary outcomes.*													

All-cause mortality rates at 90 days will be collected using NHS Digital and the Intensive Care National Audit and Research Centre.

Patient data on disease severity will be collected using the Case Mix Programme (England, Northern Ireland and Wales) and its equivalent in Scotland (Scottish Intensive Care Society Audit Group). All-cause mortality rates at 90 days will be collected using NHS Digital and equivalents in Northern Ireland and Scotland.

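### The mortality sample-size clause claims a 5% withdrawal allowance that its figures do not contain; with that loss, power for the 5.4-point margin is about 88.5%, not 90%

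*Protocol article*

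**What the plan says.** The Sample size estimate section of the protocol article states that "A total sample size of 2760 will be required" to serve both primary outcomes. For antibiotic duration it lists a 0.93-day difference, a standard deviation of 6 days, 90% power, a 5% significance level and 5% withdrawals. For safety it lists "a non-inferiority safety margin of 5.4% (using a 1-sided significance level of 2.5%, 90% power and 5% withdrawal rate". The event rate behind this safety figure is 15% deaths by day 28 in each arm. The 5% withdrawal rate is thus attached to each calculation separately. The section on randomisation says that patients are "allocated at random to PCT, CRP and usual care groups in a 1:1:1 ratio", so 2760 is 920 per arm. The section refers to Supplemental Material for detail, which is not among the documents at hand.

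**The concern.** One total is offered for two calculations with the same power and the same stated withdrawal rate, so both should rest on the same evaluable number per arm. They do not: the duration figure matches the number left after 5% loss, and the mortality figure matches the number before any loss. The mortality clause therefore states a power that its own inputs do not give.

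The primary objective makes shorter treatment acceptable only if 28-day mortality is not worsened, so this is the power statement for the comparison on which a positive conclusion depends. It is likely to be repeated in the trial report. If the mismatch came to light late, there could also be a temptation to remove it by moving the margin.

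**Working it through.** **Inputs** (Sample size estimate, and the 1:1:1 allocation):
- 2760 / 3 = 920 randomised per arm; after 5% loss, 920 × 0.95 = 874 evaluable.
- Mortality: 15% in both arms, margin 0.054, one-sided 2.5%, power 90%.
- Duration: difference 0.93 days, SD 6 days, power 90%, 5% significance level. Sidedness is not stated; two-sided is assumed.
- z-values 1.960 and 1.2816, so (1.960 + 1.2816)² = 10.507. Each comparison is taken as one biomarker arm against control at the stated level.

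**1. Duration, the plan's own figure.** n per arm = 2 × 6² × 10.507 / 0.93² = 874.7, so 875. Divided by 0.95 this is 922 per arm, 2766 in total; multiplying by 1.05 instead gives 919 per arm, 2757. Both match 2760 closely. In reverse, the detectable difference is 0.930 days with 874 per arm and 0.907 days with 920. The stated 0.93 therefore includes the withdrawals.

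**2. Mortality, without withdrawals.** n per arm = 2 × 0.15 × 0.85 × 10.507 / 0.054² = 918.9, so 919, and 3 × 919 = 2757. This matches 2760 with nobody lost.

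**3. Mortality, with the stated 5%.** 919 / 0.95 = 968 per arm (rounded up), 2904 in total: 144 more than 2760, or 5.2%. Multiplying by 1.05 instead gives 965 per arm, 2895.

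**4. What 2760 gives for mortality.** Power = Φ(0.054 / √(0.255/n) − 1.960). Margin at 90% power = 3.2415 × √(0.255/n).

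| Evaluable per arm | Power for 5.4 points | Margin at 90% power |
|---|---|---|
| 920 (no loss) | 90.0% | 5.397 points |
| 911 (1% loss) | 89.8% | – |
| 900 | 89.4% | – |
| 874 (5% loss) | 88.5% | 5.54 points |

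**5. Could rounding or another formula explain it?**
- Rounding: 5.54 would print as 5.5, not 5.4. Even an unrounded margin of 5.45 points needs 0.255 × 10.507 / 0.0545² = 902 per arm, about 2849 in total after 5% loss.
- Farrington-Manning variance: about 927 evaluable per arm, about 2929 in total after loss.
- Continuity correction: about 3017 in total after loss.
- Pooled comparison of 15% with 20.4%: 1048 per arm before any loss. Pooled 15% with 9.6%: 776 per arm, about 2451 after loss.
- Event rate: with 874 per arm, 5.4 points at 90% power would need mortality of about 14.1%, not 15%.

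No variant that includes the 5% loss gives 2760.

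**The case against.** The strongest reply is that little turns on this. The full 1.5-point drop occurs only if 28-day vital status is missing for a whole 5% of patients, and the article plans against that. Under Data collection and management, site teams follow patients into receiving hospitals and, after discharge, use health records, family doctors, patients or relatives to complete day 28; Table 1 repeats this for the primary and secondary outcomes. With 1% missing, power is 89.8%. This stands as an argument about size. It does not make the sentence true: the follow-up provisions do not address patients who withdraw consent, and the clause itself claims "using a 1-sided significance level of 2.5%, 90% power and 5% withdrawal rate".

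A second reply is that the Supplemental Material may hold a correct calculation. It may, and the article alone cannot show whether the calculation left withdrawals out or the condensed sentence attached them to mortality by mistake. On the second reading 2760 is the right number for complete mortality data and only the wording is wrong. Under either reading the printed inputs and output disagree.

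A reader might go further and infer that the trial is underpowered for safety, or that it must recruit 144 more patients. The documents do not support that. The margin, significance level, endpoint and decision rule are unaffected, and the power actually obtained depends on how complete day-28 ascertainment is.

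**Conclusion.** The mortality clause is wrong as written. On its own inputs, 2760 patients give 90% power for a 5.4-point margin only with essentially no loss; with the 5% withdrawals that the clause states, power is about 88.5% (88.2% by Farrington-Manning). The discrepancy concerns mortality only, since the duration figure reproduces with withdrawals included.

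This is a small correction to a stated power for a primary safety outcome, not a design failure. The result rests on 15% mortality in both arms, equal arms, a normal approximation and withdrawn patients contributing no mortality data. The contrast with the duration figure also rests on reading its 5% level as two-sided.

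**What to change.** Check the sentence against the Supplemental Material, keep the 5.4% margin and the 2760 patients, and make one of two changes:

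1. Restate the mortality power as about 88.5% with 5% withdrawals; or
2. Remove the withdrawal allowance from the mortality clause and say that 90% power assumes 28-day vital status is known for essentially every randomised patient. That status would come from the day-28 follow-up already described and, where consent and data access allow, from the linkage planned for later deaths ("All-cause mortality rates at 90 days will be collected using NHS Digital").

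The margin should not be widened to 5.5 points to make the arithmetic agree; that would change the safety criterion to suit the sample size.

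The first option costs one sentence. The second also commits the trial to near-complete day-28 ascertainment. The article describes linkage for 90-day mortality only and does not say whether it would supply dates of death or cover withdrawn patients, so its cost for day 28 cannot be judged from the article.
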